### Interventions

#### en_línea

It is a version of the LEARN program [25] delivered via online. It is not only a weight loss program, the main objective of *en_línea* is the acquirement of long-term healthy habits. The five treatment areas are: Lifestyle, Exercise, Attitudes, Relationships and Nutrition. We have designed and developed a website (www.programaenlinea.org) with 17 weekly treatment sessions and an exclusive mobile application for self-recording.

Participants will receive an email with two attached files to provide the instructions to use *en_línea* website and the mobile application. They will be supplied with a private username and password to access to their profiles. Weekly they will access to a new session. Session 0 is aimed to introduce the program, to get familiar with it and to self-assess the motivation level to involve in this process.

The sessions from 1 to 17 present a similar structure, but the contents are getting harder. At the first three sessions, the information is basically nutrition, physical activity and self-recording. Session 4 adds a complete explanation about the importance of social support, and provide instructions to choose a correct confidence person to help during the program. Lifestyle and attitudes contents will developed through the next sessions, when the basic components are already consolidated. Figure 2 shows an overview of the content of intervention. In the figure, the sentence “identical to previous sessions” means that the structure of each session is the same as in session 1. Nutrition and exercise are treated each week, including new aspects and consolidating the old ones.

**Fig. 2 Fig2:**
[figure not shown]
Overview of *en_línea* program content

“Set weekly goals” and “Verifying weekly goals” sections are aimed to adjust expectations and establish realistic goals. If the participants, at the end of the week, verify the accomplishment of 75% of the initial weekly goals, they will receive an automatic congratulation message and they should reward themselves.

Participants will download a mobile application designed exclusively for *en_línea*. They should record their daily meals, at least five records per day; their daily physical activity, at least their daily steps; and, their weekly weight. To count their daily steps participants will use commercial mobile applications.

Finally, once a week a specialized psychologist will provide personalized feedback about the activities of the website and the mobile application records. There is a space for this feedback at the end of each section of the website. The participant can review each activity with the corresponding feedback. Participants can send an email to the psychologist to solve doubts.

#### Standard group therapy

Participants in this arm will received a 10 sessions of standard primary care group therapy. Sessions 1 and 2 will be weekly and sessions from 3 to 10 will be biweekly. Sessions, between 8 and 10 participants, will be conducted by a specialized psychologist and they will last 90 min. Treatment areas will be the same as *en*_*línea,* beginning with nutrition and exercise and a progressive incorporation of the other topics. Material to work at home and self-recording will be provided in paper. The structure of the sessions will be: home activities and self-recording review, new information and strategies, and establishment of activities for the week. Anthropometric measures will be taken at the same time as *en_línea.*

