#### Control group

Participants in the control group only will receive a biweekly newsletter by email without feedback. They will be provided with material and instructions to self-record their daily meals and exercise. The newsletter only will content basic information about nutrition and exercise.

Follow-up sessions will take place in three arms to assess the adherence to the interventions and to evaluate the main objective of this study, the acquirement of long-term healthy habits. These face-to-face sessions will last between 15 and 30 min and will take place 1, 3, 6 and 12 months after the post treatment session. In this follow-ups, we will review: anthropometric measures, quality of life, nutrition and exercise habits.

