**Fig. 3 Fig3:**
[figure not shown]
Flow diagram of *en_línea* study

The first evaluation and follow-up visits will be conducted by the coordinator of the project and the interventions will be conducted by two psychologists. The psychologists involved are all certified general sanitary psychologist training for the interventions chosen for this investigation.

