### Statistical analysis

To estimate the sample size has been used the primary outcome, weight loss differences between baseline and post-treatment measures. The range of the effect size of the intervention will be 0.5 SD in group comparisons, alpha 5% and two-tail tests [51]. These data determine that we need at least 88 patients per group, considering an expected 31% dropout rate [52], our final choice will be *N* = 305 [53].

Analysis will be performed using STATA/IC 14.2. All data will be checked for missing values, accuracy and normality criteria. Intention to treat analysis (ITT) will be used to analyze the data, including all randomized participants. After that, per protocol analysis will be performed for participants who have completed 17 weeks follow-up. ANOVA for repeated measures, with type of intervention as independent variable and time (baseline and follow-up visits) as dependent variable, will be conducted to analyze primary and secondary outcomes.

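### Neither the named ANOVA nor the sample size allows for therapy-group clustering in the standard-therapy arm; if outcomes correlate within groups, standard errors for comparisons with that arm are too small

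*Protocol article*

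**What the plan says.** Under Standard group therapy the protocol states: "Participants in this arm will received a 10 sessions of standard primary care group therapy". It adds: "Sessions, between 8 and 10 participants, will be conducted by a specialized psychologist and they will last 90 min". The other two arms have no therapy groups. En_línea is followed individually on a website and mobile application with a psychologist's weekly feedback. For the control arm, "Participants in the control group only will receive a biweekly newsletter by email without feedback". The text after Fig. 3 says that "the interventions will be conducted by two psychologists".

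Allocation is by simple individual randomization, 1:1:1.

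The Statistical analysis section names the model as "ANOVA for repeated measures, with type of intervention as independent variable", with time as the other factor. The sample size rests on this statement: "The range of the effect size of the intervention will be 0.5 SD in group comparisons, alpha 5% and two-tail tests". It continues: "These data determine that we need at least 88 patients per group", then "considering an expected 31% dropout rate", and settles on a total of 305. The protocol nowhere mentions a therapy-group effect, an ICC, a design effect or cluster-robust errors.

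**The concern.** Patients who attend the same course of group sessions share a leader, a timetable and each other's influence, so their weight changes may be more alike than those of patients in different groups. The mean of that arm then carries between-group variation that a model with only intervention and time does not count. The design is partially nested: clustering arises after randomization and in one arm only.

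This touches a central comparison. The Background hypothesizes that en_línea will do better than, or at least as well as, standard therapy, and the primary outcome includes differences in weight loss among all three arms. With positive correlation, tests involving the group arm reject too often under the null, and the power implied by 88 independent patients is too optimistic for those tests.

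**Working it through.** **Inputs from the protocol.** Group size 8 to 10; effect 0.5 SD; two-sided alpha 5%; 88 per group; dropout 31%; total 305; allocation 1:1:1.

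**Assumptions.** ICC of weight change 0.01, 0.05 or 0.10 (none is given); fixed group membership; groups of 9, the midpoint; equal variances; even dropout across groups.

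**1. The protocol's own figure.** Power is not stated. With 0.5 SD and a two-sided 5% test, independent patients require 63–64 per arm for 80% power and 85–86 for 90%. So 88 is close to a 90% power calculation (it gives 91%) with no visible clustering allowance. The total of 305 does not follow from 88 per arm and 31% dropout: 3 × 88 / 0.69 = 383. That is a separate matter, but it means there is no slack to absorb clustering.

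**2. Structure of the group arm.** 305 / 3 ≈ 102 patients. 102 / 9 ≈ 11 groups, or about 10 to 13 over sizes 10 down to 8. The count is inferred, not stated.

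**3. Formulas.**
- Design effect in the group arm: DE = 1 + (m − 1) × ICC
- Variance ratio of a difference against an unclustered arm of equal size: V = (1 + DE) / 2
- Actual size of a nominal 5% test: 2 × (1 − Φ(1.96 / √V))

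**4. All randomized participants, m = 9.**

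| ICC | DE | V | √V | Actual size |
|---|---|---|---|---|
| 0.01 | 1.08 | 1.04 | 1.020 | 5.5% |
| 0.05 | 1.40 | 1.20 | 1.095 | 7.4% |
| 0.10 | 1.80 | 1.40 | 1.183 | 9.8% |

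Over m = 8 to 10 and the same ICC range, the actual size runs from 5.4% to 10.4%.

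**5. Completers.** 102 × 0.69 ≈ 70 patients; 70 / 11 ≈ 6.4 per group.

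| ICC | DE | V | Actual size |
|---|---|---|---|
| 0.01 | 1.05 | 1.03 | 5.3% |
| 0.05 | 1.27 | 1.13 | 6.6% |
| 0.10 | 1.54 | 1.27 | 8.2% |

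At ICC 0.05 the 70 completers carry the information of 70 / 1.27 ≈ 55 independent patients.

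**6. Power.** With about 70 completers per arm and a 0.5 SD effect, power is about 84% without clustering. With the correct standard error it is about 83% at ICC 0.01, 79% at 0.05 and between 74% and 75% at 0.10.

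**7. Scope.** Therapy groups enter only the group arm, so en_línea versus control is not affected when its error is estimated from those two arms alone.

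**The case against.** Only a condensed article is available, and a group term with its degrees-of-freedom method could sit in an unseen SAP. That lowers certainty about what will finally be done. It does not remove the point, because the article itself names the model and fixes the sample size, and neither allows for groups.

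The size is unknown. A reader might infer that the error bars are certainly too narrow by a material amount; the documents do not support that, since they give no ICC and at 0.01 the distortion is trivial. A reader might also apply the full group size of 9 to the 70 completers and conclude that they are worth only 50 patients (70 / 1.40). That ignores the dropout that reduced the arm to 70; about 55 is the consistent figure.

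The protocol gives the number of participants per session but does not say that groups are closed. If membership changes from session to session, a single effect per fixed group would not describe the correlation. This stands, and it affects the form of the model.

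Both active interventions are delivered by two psychologists, and en_línea participants receive a psychologist's feedback, so calling that arm wholly unclustered is a simplification. The calculation here covers therapy groups only, not therapist effects.

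Finally, one might extend the point to a similarity claim based on confidence intervals. The protocol hopes for at least similar results, but it states no margin and plans no such interval. The consequence that can be shown is for the planned significance tests.

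**Conclusion.** The point holds conditionally. As written, the plan understates the standard error of both comparisons with the group-therapy arm whenever the within-group ICC is positive, which is plausible for patients who attend a ten-session course together. Under the assumed ICC range, a nominal 5% test is inflated by roughly half a percentage point at the low end and to nearly 10% at the high end in all randomized participants, with somewhat less inflation among completers. These figures rest on the assumed ICCs, fixed groups of about 9 and even dropout. The protocol supports the direction of the error, not a particular size. The change should be made because it is cheap and the comparison with group therapy is central.

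**What to change.** - Record a therapy-group identifier, and any change of group, for each participant in the group-therapy arm. The article describes the trial as still recruiting, so this is easier now than reconstructing it later.
- Replace the ANOVA with a partially nested mixed model: a random therapy-group effect in the group arm only, participants in the other arms treated as unclustered, arm-specific residual variances, and Kenward-Roger or Satterthwaite degrees of freedom. Since groups form after randomization, the group effect should act on weight change or post-baseline weight.
- If membership is not fixed across sessions, adapt the group term to the actual attendance structure.
- Restate the power for the two comparisons with the group arm over a stated ICC range.

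The cost is one identifier, one model term, and somewhat wider intervals for those two comparisons. The variance component would be estimated from only about 10 to 13 groups, so it will be imprecise; this is why the small-sample degrees of freedom are needed. Fully restoring the power of 88 independent patients per arm would take about 92 to 128 analysed per arm over the assumed ranges (88 × V, with m = 8 to 10). The fix does not ask for that; it asks that the lower power be stated.

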#### Control group

Participants in the control group only will receive a biweekly newsletter by email without feedback. They will be provided with material and instructions to self-record their daily meals and exercise. The newsletter only will content basic information about nutrition and exercise.

Follow-up sessions will take place in three arms to assess the adherence to the interventions and to evaluate the main objective of this study, the acquirement of long-term healthy habits. These face-to-face sessions will last between 15 and 30 min and will take place 1, 3, 6 and 12 months after the post treatment session. In this follow-ups, we will review: anthropometric measures, quality of life, nutrition and exercise habits.

### Outcomes

#### Primary outcomes measures

The primary outcome is the weight loss. First, differences between the pre and post measures for each treatment arm. Treatment success is defined as 5–10% of weight loss respect the initial weight. Then, significant differences in weight loss and other anthropometric measures, specified later, between the three treatment arms. Finally, the maintenance of weight loss during the follow-ups, significant differences between the three treatment arms.

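### Treatment success is defined as a weight loss of 5–10%, with an upper end, so a loss above 10% does not meet the definition as written

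*Protocol article*

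**What the plan says.** The definition stands in the protocol article, Outcomes, Primary outcomes measures: "Treatment success is defined as 5–10% of weight loss respect the initial weight". The sentences around it concern a continuous quantity. The section opens with "The primary outcome is the weight loss". It continues with "First, differences between the pre and post measures for each treatment arm", and the success definition comes directly after that. The comparison between arms follows: "Then, significant differences in weight loss and other anthropometric measures, specified later, between the three treatment arms". Maintenance over the follow-up visits comes last.

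Statistical analysis bases the sample size on the same continuous quantity: "To estimate the sample size has been used the primary outcome, weight loss differences between baseline and post-treatment measures". The method named for primary and secondary outcomes is a repeated-measures ANOVA.

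No section says how a loss above 10% is classified, whether 5% is meant as a floor, or whether success is judged per participant or per arm. The Abstract gives weight loss and its maintenance as the primary outcome and mentions no success criterion.

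**The concern.** For weight loss in this population, more loss counts as a better result on the trial's own primary outcome. A success criterion should follow the same direction: a participant who does better should never move from success to non-success. A range closed at 10% breaks that. A participant who loses 9% meets the definition, and one who loses 11% does not.

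At stake is any success rate reported under this definition. As an arm's average loss grows, more of its participants pass out through the top of the range, and the rate first flattens and then drops. A reader who takes the rate at face value would think less of the better program. The wording also leaves room to settle the reading after the data are seen, and the readings can give very different rates.

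**Working it through.** The 5–10% range is not derived from other inputs, so there is no figure of the plan to reproduce. The check has two parts: what the text fixes, and how far a closed range and a floor can differ.

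**Text.** The definition gives a lower and an upper figure and uses the language of definition. In the next section, Secondary outcomes measures, adherence is written as a minimum of 80% of activities and self-records. The authors thus write a floor explicitly where they want one, and did not do so for success. Nothing elsewhere supplies the missing floor.

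**Size.** Inputs: limits of 5% and 10% (Primary outcomes measures). The mean m and the SD s of percent loss are not in the article and are assumed here; the distribution is assumed normal.

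- Floor: P(loss ≥ 5) = 1 − Φ((5 − m)/s)
- Above the range: P(loss > 10) = 1 − Φ((10 − m)/s)
- Closed range: P(5 ≤ loss ≤ 10) = floor − above

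Worked case, m = 8 and s = 5: floor = 1 − Φ(−0.6) = 72.6%; above = 1 − Φ(0.4) = 34.5%; range = 72.6 − 34.5 = 38.1%.

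| SD | Mean loss | Loss ≥ 5% | In 5–10% | Above 10% |
|---|---|---|---|---|
| 4 | 3% | 30.9% | 26.8% | 4.0% |
| 4 | 5% | 50.0% | 39.4% | 10.6% |
| 4 | 8% | 77.3% | 46.5% | 30.9% |
| 5 | 3% | 34.5% | 26.4% | 8.1% |
| 5 | 5% | 50.0% | 34.1% | 15.9% |
| 5 | 8% | 72.6% | 38.1% | 34.5% |
| 6 | 3% | 36.9% | 24.8% | 12.2% |
| 6 | 5% | 50.0% | 29.8% | 20.2% |
| 6 | 8% | 69.1% | 32.2% | 36.9% |

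Rows may be off by 0.1 through rounding.

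**Shape.** By symmetry the closed-range rate is highest when the mean sits at the midpoint, (5 + 10)/2 = 7.5%, and falls beyond it. At SD 5, a mean of 5% and a mean of 10% both give 34.1% in the range, although the floor gives 50.0% and 84.1%.

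**Differences between two means.** At SD 5, going from 3% to 5% adds 50.0 − 34.5 = 15.5 points under the floor and 34.1 − 26.4 = 7.7 points under the range. Going from 6% to 8% adds 72.6 − 57.9 = 14.7 points under the floor and 38.1 − 36.7 = 1.4 points under the range. The second pair straddles 7.5%, where the range rate is flattest, so it is close to the least favourable case.

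**Reach.** The definition does not enter the sample size, which rests on a difference of 0.5 SD in weight loss, and it does not enter the ANOVA. In both, a loss above 10% counts in full.

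**The case against.** The strongest reply is that the sentence was never meant as a closed range. A 5–10% loss can be read as a target whose working criterion is reaching 5%. It can also be read as a benchmark for an arm's average, because it follows directly on the pre–post differences per arm; the participant-level calculation would then not apply. The article names no failure category and puts nobody above 10% into one.

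These readings are possible, and the intent may well have been a floor. But the article does not state it, and the arm-level reading has the same fault: an arm averaging 11% would fall outside the definition. What stands is that the classification of losses above 10% as failures is a literal consequence of the wording, not something the article says.

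A reader might go further and infer that the success rate is part of the primary outcome, and that the definition could hide or reverse the trial's main result. The documents do not support that. The primary outcome is continuous weight loss, the planned comparison between arms is of weight loss, and no comparison of success proportions is named. Dilution or reversal could arise only in a success rate, and reversal only where at least one arm's mean loss exceeds 7.5% under the assumptions above.

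The size is also open to challenge, since mean and SD are assumed. At the low end (mean 3%, SD 4) only 4.0% of participants lie above 10%, and the two readings differ little.

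**Conclusion.** The point holds as a badly fixed definition, with a limited reach. The only success criterion in the article has an upper end, so taken literally it excludes the best results, and a rate based on it is not monotone in weight loss. Under normality with SDs of 4 to 6 and means of 3% to 8%, the share so excluded runs from about 4% to 37%; at mean 8% and SD 5 the reported rate would be 38.1% or 72.6%, depending on the reading. These figures illustrate; they do not predict, because the article gives no distribution of percent loss.

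The primary test, the sample size and the intention-to-treat comparison are untouched. This should be corrected, but it does not threaten the trial's main conclusion.

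**What to change.** Replace the success sentence in Primary outcomes measures with one saying that treatment success is a loss of at least 5% of initial weight at post-treatment (week 17), judged per participant, with no upper limit. A loss of at least 10% may be reported separately as a descriptive threshold; this is optional.

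The cost is one sentence. No new data, visits or sample-size work are needed, since the baseline and week-17 weights are already planned. Randomization and blinding states that the trial is still recruiting and that no analysis has been done, so a correction at that stage could not be driven by results.

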A randomized controlled trial (RCT) is need to examine the effectiveness of *en_línea* comparing with a standard primary care group therapy and a control group. All conditions will be described later in detail. We hypothesize that *en_línea* group will obtain better or, at least, similar effectiveness results than the standard therapy group, and better results than the control group. The primary aim of the RCT will be determine the effectiveness weight loss and maintenance of *en_línea* with the two comparison groups. The secondary objectives to determine the effectiveness of *en_línea* in comparison with the other conditions will be: a) the adherence to intervention, i.e. website tasks and mobile application records; b) number and stage of drop outs. We will conduct a 17 weeks, parallel-group, randomized controlled trial. Randomization will be performed with a simple randomization with a 1:1:1 allocation ratio. The aims of this paper are to describe the development of *en_línea* program and the protocol for the RCT.

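### The hypotheses are two specific comparisons of en_línea, but the only between-arm criterion and test stated cover any difference among the three arms

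*Protocol article*

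**What the plan says.** All references are to the protocol article.

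- **Hypotheses (Background).** The en_línea "group will obtain better or, at least, similar effectiveness results than the standard therapy group, and better results than the control group". The aim is put the same way: "The primary aim of the RCT will be determine the effectiveness weight loss and maintenance of" en_línea, set against the two comparison groups. Both statements concern one arm against each of two named comparators.
- **Between-arm criterion (Primary outcomes measures).** After the pre-post change within each arm, the section lists: "Then, significant differences in weight loss and other anthropometric measures, specified later, between the three treatment arms". For maintenance it adds: "Finally, the maintenance of weight loss during the follow-ups, significant differences between the three treatment arms". Neither item names a pair of arms or a direction.
- **Test (Statistical analysis).** One method serves primary and secondary outcomes: "ANOVA for repeated measures, with type of intervention as independent variable and time (baseline and follow-up visits) as dependent variable". The intervention factor has three levels, and time runs over baseline and the follow-up visits.
- **Sizing (Statistical analysis).** The sample size uses the weight difference between baseline and post-treatment: "The range of the effect size of the intervention will be 0.5 SD in group comparisons, alpha 5% and two-tail tests". From this, "we need at least 88 patients per group, considering an expected 31% dropout rate", with a final total of 305.

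**The concern.** The null hypothesis for a three-level intervention factor (or for its interaction with time) is that all three arms behave alike. Neither hypothesis in the Background has that null. The test can be significant because group therapy differs from control, whatever en_línea does. It can be significant when en_línea matches the newsletter arm, and also when en_línea is the worst arm.

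That situation is not far-fetched on the article's own account. The Background reports that in-person primary care programmes, including group ones, have produced weight loss, and that web programmes have had short-lived effects and low adherence compared with traditional ones. Two facts temper this. The in-person evidence is described as high-intensity, which the ten-session group arm is not said to be. The Background also says that web programmes beat control or minimal contact.

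At stake is whether the stated primary analysis answers the trial's question. If the linking contrasts are left open, the comparison that carries the conclusion can be chosen after the data are seen. The test named is also not the comparison used for sizing, which was a 0.5 SD difference in change to post-treatment.

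**Working it through.** **Inputs.** From the Statistical analysis section: effect 0.5 SD, two-sided 5%, 88 per group, 31% dropout, N = 305. From Randomization and blinding: allocation 1:1:1. Power is not stated. Assumed here: the outcome is weight change from baseline to post-treatment, with a common SD of 1. With two time points, the group-by-time test of a repeated-measures ANOVA is the same as a one-way F test on change.

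**Step 1: what the 88 corresponds to.** For a two-sample t-test with d = 0.5 and n = 88 per arm, the noncentrality is 0.5 × √(88/2) = 3.317 on 174 df. Power at two-sided 5% is 0.910. Solving for 90% power gives 86 per arm (85 by the normal approximation). So 88 fits a pairwise comparison at about 90% power, if that was the target.

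**Step 2: numbers per arm.** Either 88 per arm as planned, or what remains of 305 after 31% dropout: 305 × 0.69 / 3 = 70.15, about 70 per arm. (The total of 305 does not follow from 88 per group and 31%: 264 / 0.69 gives 383. That is a separate matter, and nothing here depends on it.)

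**Step 3: three-arm F test when only group therapy differs.** Means are (en_línea, control, group therapy) = (0, 0, d) in SD units. The noncentrality is n × Σ(mean − grand mean)² = n × d² × 2/3, with 2 and 3n − 3 df and alpha 0.05.

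| d (SD) | n per arm | Noncentrality | P(F test significant) |
|---|---|---|---|
| 0.5 | 88 | 88 × 0.25 × 2/3 = 14.67 | 0.936 |
| 0.5 | 70 | 70 × 0.25 × 2/3 = 11.67 | 0.869 |
| 0.3 | 88 | 88 × 0.09 × 2/3 = 5.28 | 0.522 |
| 0.3 | 70 | 70 × 0.09 × 2/3 = 4.20 | 0.428 |

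A simulation of 20,000 trials at d = 0.5 gave 0.936 and 0.867.

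**Step 4: what a direct contrast does in the same trials.** In that simulation, a two-sided 5% test of en_línea against control found en_línea superior in about 2.4% of trials (2.5% at 88 per arm, 2.4% at 70), as it should when the two arms are equal. The F test was significant without en_línea beating control in 91% of trials at 88 per arm and 84% at 70.

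**Step 5: power of the two contrasts at 0.5 SD.** At the full 5%, as for each test in a fixed order taken on its own: 0.91 with 88 per arm, 0.84 with 70. At 2.5% each (Bonferroni): 0.85 and 0.75.

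**The case against.** The strongest defence is that the article states no decision rule. The outcomes section lists measures and the analysis section names a model. Neither mentions an omnibus or F test, and neither says that a significant three-arm result will be read as en_línea beating control. Differences between three arms can be shorthand for differences between pairs, and the sizing text, with 88 per group fitting a two-sample test, points that way. Each arm's pre-post change is also to be examined, so a failing en_línea arm would be visible. Contrasts may stand in an analysis plan that is not shown. With exactly three arms, an F test followed by unadjusted pairwise tests controls the familywise error.

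Much of this stands. A reader might infer that the investigators will claim superiority from the F test alone; the article does not say so. A reader might also set 0.94 against 0.05 as an inflated error rate. That would be wrong: with group therapy truly different, the global null is false and rejecting it is correct.

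What does not stand is that this is only missing detail. The article fixes the between-arm criterion, twice, as a difference among three arms, and names a test over all visits. Contrasts added elsewhere would have to replace that criterion or take precedence over it. If the pairwise reading was intended, saying so removes the ambiguity.

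**Conclusion.** The point holds in a limited form. The stated between-arm criterion and test are not specific to en_línea, while both hypotheses are, and the test named is not the comparison used for sizing. A significant result for the three-level factor does not by itself support either hypothesis. With en_línea equal to control, it would be significant with probability about 0.87 to 0.94 if group therapy were 0.5 SD better, and about 0.43 to 0.52 if it were 0.3 SD better.

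These figures assume a one-way F test on baseline-to-post-treatment change, equal arm sizes of 70 or 88, a common SD, and a group-therapy effect of the stated size. A smaller effect lowers them. They measure lack of specificity and do not show that a false claim will be made. The change should be made, since a better-aimed analysis is available and the article says that recruitment is under way and no analysis has been done.

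**What to change.** In Primary outcomes measures and Statistical analysis:

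1. Name as the primary analysis two planned contrasts of mean weight change from baseline to week 17: en_línea minus control, and en_línea minus standard group therapy. Report each with its estimate and 95% CI.
2. Prespecify a multiplicity rule. A fixed order with control first is one option and splits no alpha; Bonferroni at 2.5% each is another.
3. Report the same two contrasts at the 1, 3, 6 and 12 month follow-ups for the maintenance aim.
4. Keep the three-arm repeated-measures ANOVA as supportive, and base any claim about en_línea only on its own contrasts.

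The cost is wording, with no extra patients or data. Under a fixed order, the group-therapy contrast cannot be claimed if the control contrast fails. Under Bonferroni, power per contrast falls as shown in Step 5. A difference test against group therapy does not establish similarity, so that part of the hypothesis needs separate treatment.
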